## Abstract

**Background:**

Epileptic seizures are common clinical features in patients with acute subdural hematoma (aSDH); however, diagnostic feasibility and therapeutic monitoring remain limited. Surface electroencephalography (EEG) is the major diagnostic tool for the detection of seizures but it might be not sensitive enough to detect all subclinical or nonconvulsive seizures or status epilepticus. Therefore, we have planned a clinical trial to evaluate a novel treatment modality by perioperatively implanting subdural EEG electrodes to diagnose seizures; we will then treat the seizures under therapeutic monitoring and analyze the clinical benefit.

**Methods:**

In a prospective nonrandomized trial, we aim to include 110 patients with aSDH. Only patients undergoing surgical removal of aSDH will be included; one arm will be treated according to the guidelines of the Brain Trauma Foundation, while the other arm will additionally receive a subdural grid electrode. The study’s primary outcome is the comparison of incidence of seizures and time-to-seizure between the interventional and control arms. Invasive therapeutic monitoring will guide treatment with antiseizure drugs (ASDs). The secondary outcome will be the functional outcome for both groups as assessed via the Glasgow Outcome Scale and modified Rankin Scale both at discharge and during 6 months of follow-up. The tertiary outcome will be the evaluation of chronic epilepsy within 2–4 years of follow-up.

**Discussion:**

The implantation of a subdural EEG grid electrode in patients with aSDH is expected to be effective in diagnosing seizures in a timely manner, facilitating treatment with ASDs and monitoring of treatment success. Moreover, the occurrence of epileptiform discharges prior to the manifestation of seizure patterns could be evaluated in order to identify high-risk patients who might benefit from prophylactic treatment with ASDs.

**Trial registration:**

ClinicalTrials.gov identifier no. NCT04211233.

## Background

Epileptic seizures are one of the frequent complications seen in patients with traumatic brain injury; the incidence is approximately 20% [1]. In particular, acute subdural hematoma (aSDH) is one of the most important predictors for seizures—alongside other parameters like age, preoperative Glasgow Coma Scale score, cerebral herniation, hematoma volume, and time to operation—associated with worse neurological outcome [2–8]. In a recent systematic review, the mean incidence of seizures in aSDH was 28%, whereas one retrospective study focusing on diagnostic electroencephalography (EEG) reported a very high incidence of epileptiform discharges on surface EEG scans in 87% of patients with aSDH. Thus, the question arises as to whether the incidence of seizures is underestimated [8, 9].

Despite the successful evacuation of subdural hematoma, approximately one third of patients show no clinical improvement without any medical explanation as to why. Surface spot EEG is routinely performed to detect seizures; however, the sensitivity of this approach is limited due to the skin–bone barrier and the short duration of recording. Furthermore, surface EEG is not always available as a diagnostic tool—for example, during the night or on weekends—which is an additional limitation leading to lengthier time to treatment. Spot surface EEG only records for 20 to 30 min in contrast with continuous EEG recordings which are performed for hours or days.

Due to the clinical relevance of seizures, several studies have investigated the benefit of prophylactic treatment with antiseizure drugs (ASD) [9, 10]. To date, there is only one recommendation from the Brain Trauma Foundation ruling evidence class II for treating patients with severe traumatic brain injury (TBI) with prophylactic ASD treatment during the first week based on data from Temkin et al. [11]. Beyond this time window, there was no clinical benefit for patients selected. Still, there are some limitations of the study in that the clinical use of prophylactic ASD treatment varies between clinicians and countries. In the 1980s, the standard medication was phenytoin, which has several side effects but by now several new intravenous antiepileptic drugs with comparable efficacy but better safety profiles have been introduced. Temkin et al. also did not distinguish between high-risk seizure-prone patients, like patients with aSDH, and low-risk patients, which is one of the limiting factors in supporting a more general recommendation on the treatment with ASDs. Therefore, the role of prophylactic ASD treatment is still questionable.

In the presurgical epilepsy evaluation, invasive EEG electrodes are commonly used to delineate the seizure-onset zone. The benefit of these electrodes relative to routine surface EEG is the possibility of real-time analysis in the case of seizure occurrence. It also enables direct monitoring of therapeutic effects. Therefore, the idea of this study was to make real-time analysis feasible in patients with TBI, particularly aSDH, to promote improved diagnostic and therapeutic real-time monitoring for detecting subclinical or nonconvulsive seizures.

### Study goals and objectives

Thus far, to our knowledge, no clinical study evaluating or monitoring seizures in patients with aSDH has been conducted. The surgical treatment of aSDH offers the unique opportunity to implant subdural EEG electrodes safely on sight and during the course of an already necessary surgical intervention, in order to demonstrate the potential benefits of invasive EEG in real-time, such as the earlier detection of seizures enabling faster therapeutic treatment and simultaneous therapeutic monitoring. The goal of the study is to evaluate the diagnostic and therapeutic effect of subdural invasive EEG monitoring to develop a standard treatment guideline for aSDH.

## Methods/design

### Trial design

This is a prospective nonrandomized controlled study (phase I trial) where eligible participants will be divided into two arms: one intervention arm and one control arm. Enrollment, allocation, analysis and follow-up were summarized as a flow chart (Fig. 1).

**Fig. 1 Fig1:**
[figure not shown]
DISEASE study protocol flowchart

### Study setting and inclusion/exclusion criteria

Patients will be recruited from the Department of Neurosurgery, University Hospital Frankfurt am Main following a diagnosis of aSDH. The local neurosurgical teams review patients upon admission and will assess eligibility for inclusion in the DISEASE trial. If informed consent is obtained and a mobile EEG system is available for recording, patients will be recruited into the intervention arm. Otherwise (e.g., a mobile EEG system is not available because it is already in use for the recording of other patients), patients will be placed in the control arm for follow-up.

This study will include adult patients (aged ≥18 years) with symptomatic aSDH requiring operative treatment via craniotomy or craniectomy who provided informed consent. Patients with infaust prognosis, asymptomatic patients with conservative treatment, those with aSDH as a secondary diagnosis, and those with concurrent enrollment in any other trial will be excluded.

### Informed consent

If the patient is able to consent, the neurosurgical staff member will explain the study design and further procedures to them. Written informed consent from the patient has to be obtained prior to the implantation of any invasive subdural electrodes. If the patient is unable to consent, a patient representative or independent physician may consent on behalf of the patient. Thereafter, if the patient’s clinical situation improves, consent should be sought from them at a later time.

### Trial interventions

The surgical procedure is standardized for both arms. All patients with aSDH will undergo the surgical evacuation of hematoma via craniotomy or craniectomy and receive subdural drain as well as an intracranial pressure monitoring probe. One arm would additionally receive a subdural EEG electrode with continuous monitoring (intervention arm), while the other arm would be treated with the standard treatment (control arm) according to the guideline from Brain Trauma Foundation as follow:

Treatment:
Hyperventilation only as a temporizing measure to reduce ICP with maximum PaCo2 of 30 mmHg (evidence IIb)Barbiturate administration only to control elevated ICP refractory to maximum standard medical and surgical treatment (evidence IIb)Early tracheotomy in case of inadequate recovery (evidence IIa)Feeding patients to attain basal caloric replacement at least by the fifth day (evidence IIa)Low molecular weight heparin for the deep vein thrombosis prophylaxsis

Monitoring:
Intracranial pressure monitoring (<22 mmHg) (evidence IIb)Cerebral perfusion pressure monitoring (60-70 mmHg) (evidence IIb)Systolic blood pressure >100 mmHg (evidence III)

The subdural EEG electrode (PLATIN 1 × 4 or 1 × 6; Ad-Tech Medical Instrument Corporation, Oak Creek, WI, USA) will be intraoperatively implanted in the subdural space frontotemporally and diverted separately from the wound area (Fig. 2). Next, a postoperative CT scan will be performed and all patients will be monitored in the intensive care unit (Fig. 3).

**Fig. 2 Fig2:**
[figure not shown]
Intraoperative situs after the evacuation of acute subdural hematoma and insertion of two Jackson–Pratt drains (*), intracranial pressure probe (#) and frontotemporally placed subdural EEG electrode (§)

**Fig. 3 Fig3:**
[figure not shown]
**a** Postoperative scout of CT scan with frontal EEG electrodes. **b** Coronary reconstruction of the CT scan. **c** Postoperative scout of CT scan with temporal EEG electrodes. **d** 3D reconstruction of the CT-scan

As a clinical parameter, GCS will be evaluated every day and surface EEG will be performed at least once during the first 7 days post-operation in all patients. Additional surface EEGs will be performed if there is a suspicion of seizure. In the intervention arm, the continuation of invasive EEG monitoring will be evaluated by a board-certified epileptologist (Fig. 4). If a seizure is detected on EEG, treatment with benzodiazepines and ASDs will be started under further EEG monitoring and in consideration of the patient’s clinical condition. Treatment with ASDs will be adjusted on demand according to clinical and EEG assessment. If treatment with benzodiazepines and intravenous ASD is deemed insufficient for seizure suppression, escalation of treatment with anesthetics to obtain a seizure suppression or burst suppression pattern under EEG monitoring would be considered. The maximum period of invasive monitoring is set at 7 days, at which point the electrode should be removed. The subdural EEG electrode is removed simply by drafting as a normal wound drain and the incision sutured with Premilene 3.0 (Braun Melsungen AG OPM, D-34212 Melsungen, Germany).

**Fig. 4 Fig4:**
[figure not shown]
Subdural four-channel EEG recording showing diffuse slowing (**a**), epileptiform discharges (**b**) and a continuous seizure pattern (**c**)

### Definition of seizure

Seizure are defined as recommended by the International League Against Epilepsy, either as documented clinical seizure manifestation, ictal pattern in the EEG recordings, or clinical suspicion with interictal epileptiform discharges in the EEG recordings in temporal relationship with acute brain insult.

### Timeline

The anticipated timeline for study participants is as follows:
Patient admission with aSDHInformed consent obtained (interventional arm/control arm)Operative treatment of hematoma via craniotomy/craniectomy either with or without placement of subdural EEG electrodeMonitoring in intensive care unitPostoperative CT control 24 h laterClinical assessment as part of the routine standard of care (e.g., GCS, neurological status, routine laboratory tests)Three to seven days of invasive EEG monitoring by a board-certified epileptologistOptional spot surface EEG, usually between Days 1 and 7Removal of subdural EEG electrode at Day 7Patient discharge after clinical evaluationOutpatient clinical evaluation at 6 months postoperatively.Evaluation of chronic epilepsy at follow-up in 2–4 years

### Trial outcomes measures

The primary and secondary outcome measures for this study are as follows:

Primary outcome measure:
Incidence of seizure and time between surgery and seizure detection

Secondary outcome measures
Functional and neurological outcomes (e.g., modified Rankin scale, Glasgow outcome scale) at discharge and for 3 to 6 months postoperativelyTherapeutic effects and benefits attributable to invasive monitoring and ensuing treatment (time to first interictal epileptiform discharges, occurrence of seizure patterns and progression of seizures to status epilepticus)Complication rate of the interventionPredictors for the development of early and late epileptic seizuresLongterm Follow-up for evaluation of chronic epilepsy (2–4 years)

All measures will be performed by the staff members of DISEASE-tiral. Independent from the study, all patients are scheduled for an outpatient clinic appointment in 6 months for clinical follow-up. Otherwise, the follow-up data will be retrieved by a phone call from the responsible study investigators. The long term follow-up will be performed accordingly.

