### Statistical analysis and sample size

The IBM SPSS Statistics version 25 software program (IBM Corp., Armonk, NY, USA) will be used for data analysis. Data will be described using means ± standard deviations and numbers of patients, including percentages for continuous and categorical variables. For parametric parameters, an unpaired t-test will be used. For nonparametric parameters, variables will be analyzed in a contingency table using either Fisher’s exact test or the chi-squared test as appropriate. To assess the impact of the variables, odds ratios with 95% confidence intervals will be calculated. A *p*-value of 0.05 or less is considered to be statistically significant and all tests will be two-tailed.

When estimating the sample size with consideration of increased seizure detection by invasive EEG monitoring, the difference in the incidence rate is assumed to be 20%. The sample size was calculated as 110 patients (*n* = 55 patients each arm) to ensure 80% power (1-ß = 0.8). Moreover, time-to-event analysis will be performed to detect the timeline until seizure detection.

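### The primary outcome is a pair with no order or success rule, each part judged at 0.05 and only incidence sized; the error inflation is small unless a t-test is also run on detection times

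*Protocol article*

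**What the plan says.** Under Trial outcomes measures, the primary outcome is "Incidence of seizure and time between surgery and seizure detection". The Methods part of the abstract likewise says that the "primary outcome is the comparison of incidence of seizures and time-to-seizure between the interventional and control arms". Neither place ranks the two parts or says whether one or both must succeed.

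The section Statistical analysis and sample size contains four relevant statements:

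- **Threshold.** A p-value of "0.05 or less is considered to be statistically significant and all tests will be two-tailed". No split, order or exception is given for the primary pair.
- **General methods.** "For parametric parameters, an unpaired t-test will be used". For what the article calls nonparametric parameters, "variables will be analyzed in a contingency table using either Fisher’s exact test or the chi-squared test as appropriate".
- **Seizure timing.** "time-to-event analysis will be performed to detect the timeline until seizure detection". The particular test is not named.
- **Sample size.** The article states that "the difference in the incidence rate is assumed to be 20" percent, and derives 110 patients (55 per arm) for 80% power. No effect size or power is given for time to detection.

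**The concern.** Two quantities share primary status, and each can be declared significant at 0.05. Because no rule says what counts as success, that choice could be made after the data are seen: either part, both parts, or whichever method gives the smaller p-value. The stated 80% power refers to incidence only, so a reader cannot tell how well the trial is placed to answer the timing half of its primary question.

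A second uncertainty concerns method. Time from surgery to detection is a continuous quantity, and the general t-test rule could be read as covering it. A t-test on detection times needs a detection time, so it can use only patients with a detected seizure. Membership of that group is the other half of the primary outcome. The electrode is also expected to reveal subclinical or nonconvulsive seizures, so the detected groups in the two arms may contain different kinds of seizure. A difference in mean detection time between them would not be a comparison of the arms.

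**Working it through.** **1. What the 110 patients cover.** The stated inputs are a difference of 0.20, power of 80%, two-sided 0.05 and equal arms. The control rate is not stated, so 110 cannot be derived from these inputs alone. The usual formula with pooled variance is

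n per arm = [1.960·√(2·p̄·(1−p̄)) + 0.842·√(p₁(1−p₁) + p₂(1−p₂))]² / 0.20².

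- Assumed 7% vs 27%: [1.960·√0.2822 + 0.842·√0.2622]² / 0.04 ≈ 54.2, rounded up to 55. This matches the plan's figure.
- 28% vs 48%, taking the article's background incidence of 28% as the control rate: [1.960·√0.4712 + 0.842·√0.4512]² / 0.04 ≈ 91.3, rounded up to 92. With 55 per arm, power is about 58%.

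The missing control rate is a separate matter. What counts here is that every input concerns incidence and none concerns time.

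**2. Simple bounds if either part may succeed.** Two independent tests at 0.05 give 1 − 0.95² = 9.75%. Three would give 1 − 0.95³ = 14.3%. The tests here are correlated, so these are reference values only.

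**3. Simulation under no difference.** Assumptions: 55 per arm, a seven-day window, exponential seizure times, no deaths, 20,000 trials per setting, each test at 0.05. The t-test uses only patients with a seizure inside the window.

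| Overall incidence | Chi-squared or log-rank | Chi-squared or t-test | Any of the three |
|---|---|---|---|
| 17% | 5.3% | 10.1% | 10.3% |
| 28% | 5.5% | 9.9% | 10.3% |
| 38% | 5.6% | 9.8% | 10.3% |

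At 20,000 trials the Monte Carlo standard error near 5.5% is √(0.055·0.945/20,000) ≈ 0.16 percentage points. Extending the range to 48% incidence gives 5.3 to 6.0% for chi-squared or log-rank, and 9.6 to 11.0% once the t-test is included.

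The pattern has a simple explanation. Chi-squared and log-rank use largely the same events, so the second test adds little. In this model, the timing among detected cases is independent of how many cases there are, so chi-squared plus the t-test behaves almost like two independent tests (9.75%).

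**4. Effect of using Fisher's test**, which the article equally allows. At 28% and 48% incidence, Fisher or log-rank gives 4.9% and 5.6%; Fisher or t-test gives 8.1% and 8.0%.

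**5. Patients a t-test would use.** At 28% incidence, 0.28 × 110 ≈ 31 patients have a detection time. The other 79 or so (72%) drop out of that comparison.

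**6. Splitting alpha instead of ordering.** At 0.025 per part and the assumed 7% vs 27%, 66 per arm are needed, and 55 per arm gives 71.6% power rather than 80.6%. An ordered procedure avoids this loss.

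**The case against.** A reader might infer that the plan, as written, carries a 10% false positive rate across three tests. The document does not support that. The t-test appears only as a general rule, while the one sentence on seizure timing names a time-to-event analysis, and the specific statement is the more natural reading. A time that is censored in everyone without a seizure is also not an obvious candidate for a t-test. With the methods most naturally assigned, the inflation is at most about one percentage point, and with Fisher's test it can vanish. This objection stands, and it limits the size of the point.

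It can also be said that the abstract speaks of one primary outcome. If both parts had to succeed, false positives would not be inflated at all. That is correct, but the joint power could then not exceed the power for incidence, and the article does not state that rule either.

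Third, an analysis plan that is not shown might settle the order of testing. Method detail such as log-rank or Cox can properly be left there. The point rests instead on what this article itself fixes: two primary quantities, one threshold for all tests, and a sample size for one of them.

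Finally, the trial is single-centre, nonrandomized and labelled phase I, with a randomized trial to follow and selection bias acknowledged. That lowers the practical weight of a small error inflation. It does not remove the need to say which result decides the primary question.

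**Conclusion.** The point holds as a minor one. The primary outcome is a pair without an order or a success rule, every test is judged at 0.05, and the sample size covers incidence only. If success on either part counts, the false positive rate is about 5.3 to 6.0% with chi-squared plus log-rank. It reaches about 10% only if chi-squared is used and the general t-test is also applied to detection times, a use that the text neither assigns nor excludes.

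These rates assume 55 per arm, a seven-day window, exponential times and 17 to 48% incidence. The objection to a t-test among detected cases does not depend on the simulation, because it would compare selected subsets whatever the error rate.

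**What to change.** - Name seizure incidence, the outcome that was sized, as the single primary outcome, and state its window. Day 7 is a natural proposal because it is the maximum period of invasive monitoring and the period in which every patient is to have at least one surface EEG. It is not in the sample size text, so the investigators must adopt it explicitly.
- Test time to detection second, at 0.05, only if incidence is significant. When neither part truly differs, a false positive then requires incidence to be significant first, so the rate stays at the 5% level of that test, and incidence keeps its full 0.05.
- Analyse time in all patients from surgery, by a log-rank or cause-specific Cox test, with death as a competing event.
- State that the unpaired t-test is not used for detection times.

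The cost is a few sentences. No patients need to be added for multiplicity, and the times of operation and seizure are already collected. The real downside is that time to detection is formally tested only after incidence; if incidence is not significant, the timing result is descriptive.

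### Three secondary measures labelled as therapeutic benefit depend on how much EEG each arm receives, so they cannot show a treatment effect in either direction

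*Protocol article*

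**What the plan says.** The stated aim has two halves: "The goal of the study is to evaluate the diagnostic and therapeutic effect of subdural invasive EEG monitoring" (Study goals and objectives). Under Trial outcomes measures, one secondary bullet is presented as the therapeutic effect and benefit of invasive monitoring and the treatment that follows. It is filled by "time to first interictal epileptiform discharges, occurrence of seizure patterns and progression of seizures to status epilepticus". No denominator, time window or test is given for progression. Functional outcome (modified Rankin and Glasgow Outcome scales) and long-term epilepsy are separate secondary outcomes.

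Four other statements bear on how these measures behave:

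- **What counts as a seizure.** An "ictal pattern in the EEG recordings" is sufficient on its own (Definition of seizure).
- **EEG exposure.** The intervention arm has continuous subdural recording (Trial interventions) for three to seven days (Timeline). What both arms share is that "surface EEG will be performed at least once during the first 7 days post-operation in all patients" (Trial interventions, text after Fig. 3), with more on suspicion. The Timeline calls the spot EEG optional. "Spot surface EEG only records for 20 to 30 min" (Background).
- **Expected effect on detection.** In the sample size paragraph, with increased detection given as the reason, "the difference in the incidence rate is assumed to be 20" per cent.
- **Limits of surface EEG.** The Abstract says of it that "it might be not sensitive enough to detect all subclinical or nonconvulsive seizures or status epilepticus".

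**The concern.** An outcome that is to show therapeutic benefit should stay the same in both arms when treatment has no effect. These three do not have that property.

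An interictal discharge or a seizure pattern is seen only while EEG is running. The arm recorded for days will show earlier first discharges and more patterns whatever treatment achieves. Read as treatment outcomes, those differences would look like harm. Read as findings of the electrode, they are diagnostic yield.

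Progression to status epilepticus is the measure most likely to be read as clinical benefit. If it is taken among patients with a detected seizure, the two groups compared are selected differently, because the intervention decides who enters one of them. Extra seizures that do not go on to status enlarge the denominator in the electrode arm only. Extra nonconvulsive status seen only by the electrode enlarges the numerator in that arm only.

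The study is meant to inform a treatment guideline and a later randomized trial, so a detection artefact reported as therapeutic benefit would be carried forward.

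**Working it through.** **Inputs from the protocol article.** Detection difference 20 percentage points (my reading of the 20%); 55 patients per arm; background seizure incidence about 20% in traumatic brain injury and 28% in acute subdural hematoma; spot EEG 20 to 30 min; invasive monitoring 3 to 7 days. **Assumed, because the article gives none:** the control-arm detection rate p and the rate of status epilepticus.

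**The plan's own figure.** The total of 110 can be neither confirmed nor refuted without a control rate. A two-sided 5% test of two proportions without continuity correction, at 80% power, gives 55 per arm at about 7% against 27% (or the mirror, about 73% against 93%). The background rates give 82 per arm (20% against 40%) or 92 (28% against 48%). The point here does not depend on 110; the check shows only that p must be assumed.

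**Step 1, exposure.** Three days is 3 × 24 × 60 = 4,320 min. Against one spot EEG that is 4,320/30 = 144 to 4,320/20 = 216 times the recording time. One spot EEG is the minimum, so the true multiple is lower in patients who have more.

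**Step 2, no treatment effect and no status among the extra detections.** Let s be status epilepticus per patient, equal in both arms and fully detected. Progression among detected seizures is s/p in control and s/(p + 0.20) with the electrode. The ratio is p/(p + 0.20), whatever s is. The illustration assumes 3 status cases per arm:

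| Control p | Electrode | Ratio | Among detected seizures | Among all 55 |
|---|---|---|---|---|
| 28% | 48% | 0.28/0.48 = 0.58 | 3/15.4 = 19% v 3/26.4 = 11% | 5.5% v 5.5% |
| 20% | 40% | 0.20/0.40 = 0.50 | 3/11 = 27% v 3/22 = 14% | 5.5% v 5.5% |
| 8% | 28% | 0.08/0.28 = 0.29 | 3/4.4 = 68% v 3/15.4 = 19% | 5.5% v 5.5% |

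**Step 3, the electrode also finds status.** Let f be the share of the extra detected patients who have status epilepticus. The electrode-arm rate is (s + 0.20f)/(p + 0.20). Setting it equal to s/p gives f = s/p, so the bias reverses once f exceeds the control arm's own progression rate. With p = 20% and s = 5%, control progression is 5/20 = 25%:

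| f | Electrode, among detected seizures | Electrode, among all patients (control 5%) |
|---|---|---|
| 0% | 5/40 = 12.5% | 5% |
| 10% | 7/40 = 17.5% | 7% |
| 25% | 10/40 = 25% | 10% |
| 40% | 13/40 = 32.5% | 13% |

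The last column shows that an all-patient denominator alone is not enough. It removes the dilution, but status that only the electrode can see still raises the electrode arm's rate.

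**The case against.** The strongest reply is that the article never states the denominator. It is a condensed account, and a full protocol or analysis plan could define status epilepticus per patient. That stands: the detected-seizure denominator is an inference from the wording. It does not rescue the measure, because step 3 shows a per-patient rate is also distorted when status is unequally detected.

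A reader might infer three stronger things that the document does not support.

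- *The progression rate must fall, producing false benefit.* This needs the extra seizures to contain little or no status. Nothing says they are mild, and the Abstract says surface EEG may miss status as well.
- *A spurious reduction of 42% (1 − 0.58) is to be expected.* That figure needs a 28% control rate, which is a literature mean and not a planning assumption, and full detection of status in both arms. Nor would such a difference often be significant. With 3 status cases per arm, Fisher's exact test gives p = 0.38 (3/11 v 3/22) or 0.65 (3/15 v 3/26); with 8 per arm, 0.07 or 0.19.
- *The therapeutic half of the goal goes unanswered.* Functional outcome in both arms is already a secondary outcome, and the Abstract names it as the secondary outcome.

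It is also fair to say that the bullet covers monitoring as well as treatment, so diagnostic findings have a place in it. But it then joins diagnostic and therapeutic results under one label of benefit, and that is the difficulty.

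**Conclusion.** The point holds in a limited form and is a cheap improvement. The protocol article itself names these three measures and labels them therapeutic benefit, while giving the arms very different chances of observing them. They can therefore differ with no treatment effect, whichever denominator is used.

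For progression among detected seizures, the ratio from detection alone is 0.50 to 0.58 at assumed control rates of 20% to 28%, if the extra detections include no status. It rises to 1 when the share with status among the extra detections equals the control progression rate, and exceeds 1 beyond that. The size and the sign both depend on quantities the article does not give. The measure therefore cannot show therapeutic benefit or harm.

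**What to change.** Amend the secondary outcome as follows:

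1. Report status epilepticus as a proportion of all enrolled patients in each arm.
2. Record the mode of detection for each seizure and each status episode: clinical, surface EEG, or electrode only. The parameters listed in the article include the timing of seizure but not how it was found.
3. Base any between-arm therapeutic comparison on status detected clinically or by surface EEG, the methods available in both arms, and on the modified Rankin and Glasgow Outcome scales already planned.
4. Report electrode-only status, time to first interictal discharge and occurrence of seizure patterns as diagnostic yield of the intervention arm.

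The cost is one extra data field, revised outcome wording and possibly a less favourable apparent result. Some imbalance remains, because surface EEGs beyond the first are prompted by suspicion and their number may differ between arms. Reporting that number per arm would show how far this matters.
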